## Abstract

**Context:**

Substance use disorders (SUDs) are highly prevalent among inpatient adolescents with psychiatric disorders. In this population, substance use and other psychiatric outcomes can reinforce one another. Despite the need for integrated interventions in youths with dual diagnoses, few specific instruments are available. App-based technologies have shown promising results to help reduce substance use in adolescents, but their applicability in youths with associated severe psychiatric disorders is poorly documented. We aim to evaluate the feasibility of an ecological momentary assessment (EMA) intervention for all substance users, and of a smartphone application for cannabis users (Stop-Cannabis), for outpatient treatment after hospital discharge.

**Methods and analysis:**

All inpatient adolescents with psychiatric disorders hospitalized between 2016 and 2018 in a university hospital will be systematically screened for SUD and, if positive, will be assessed by an independent specialist addiction team. Participants with confirmed SUDs will be invited and helped to download an EMA app and, if required, the Stop-Cannabis app, the week preceding hospital discharge. Information about the acceptability and use of both apps and the validity of EMA data in comparison to clinical assessments will be assessed after 6 months and 1 year.

**Discussion:**

This research has been designed to raise specific issues for consideration regarding the sequence between substance use, contextual factors, and other psychiatric symptoms among adolescents with comorbid severe psychiatric disorders. A better understanding of the mechanisms involved will inform the development of integrated treatment for dual disorders at that age.

**Ethics and dissemination:**

The study has already been approved and granted. Dissemination will include presentations at international congresses as well as publications in peer-reviewed journals.

**Trial registration:**

European Clinical Trials Database: Number 2016-001999-30.

## Introduction

### Background

#### Substance Use Disorders and Psychiatric Disorders in Adolescents

Psychiatric comorbidity in adolescents who abuse substances is the rule rather than the exception, with 61–88% having a dual diagnosis (1, 2). The coexistence of both disorders is associated with important disruptions in a range of functional domains, including academic attainment, social and family relationships (2, 3), and accidents (4). In addition, initiation of substance use at a younger age (5) and a faster relapse after treatment (6) are reported in youths with preexisting mental health problems. In turn, the natural course of psychiatric disorders may be affected by substance use, either due to negative psychosocial consequences associated with substance involvement (7) and/or to the direct effect of the substance on the central nervous system (8). In youths with mood or psychotic disorders, for example, daily use of cannabis is associated with a more severe clinical presentation, impaired cognitive and interpersonal abilities, and poorer responses to pharmacological treatments (9). The development of integrative treatment for substance use disorders (SUDs) and psychiatric disorders is therefore a priority (10, 11).

Among adolescents hospitalized for a psychiatric problem, 17–50% meet criteria for one or more SUDs (12–17). In a previous study of adolescents hospitalized in three psychiatric units in France, most subjects met criteria for a non-nicotine SUD: around 70% for cannabis, 60% for alcohol, and 20% for other substances (18). Unsurprisingly, those with dual disorders exhibited more severe clinical characteristics (e.g., more suicide attempts) and a higher level of functional impairment (e.g., more school absenteeism) than patients without SUDs. They also received more diagnoses of axis 2 comorbidities and were exposed to more severe psychological contexts (e.g., maltreatment or loss of a first relative) (18). Given the high prevalence of SUDs among adolescents who are hospitalized, and the poor clinical outcomes due to the negative interplay between both disorders, specific preventive interventions for addiction should be developed and evaluated in this population.

#### Addiction Preventive Interventions in Inpatient Adolescents with Psychiatric Disorders

It is well established that treatments for SUDs and psychiatric disorders are less effective when provided separately (1, 6). Although the efficacy of integrated approaches for the management of dual disorders has been demonstrated in adolescents (10, 11), there is some concern that – in practice – the so-called “integrated approach” often consists of the addition of evidence-based treatments for both problems, with too few specific dual diagnostic or therapeutic tools. For example, in order to choose the optimal treatment, the sequence between substance use and other psychiatric symptoms in patients’ daily life should be explored, but we are not aware of any tool that would measure this pattern. Furthermore, treatment compliance is a key prognostic factor in addiction. For most teenagers, SUDs are commonly under-recognized as a health issue (19). The development of tools that promote better recognition of patients’ problems with substances, and enhance behavior change, would therefore be worthwhile. Digital approaches may be a promising avenue for health-related interventions among adolescents given their propensity to use digital technologies (20–24).

#### Digital Approaches

The uptake of smartphones in the general population has encouraged the development of apps used to facilitate real-time assessment of the patient in his/her natural environment [Ecological Momentary Assessment (EMA)] and allowed delivery of smartphone app interventions in this context.

Ecological momentary assessment consists of using computers or other devices to collect self-assessments repeatedly in real-time, in various situations of the participant’s daily life, either for research purposes or to provide participants with timely feedback and advice (25). Different terms have been used for this methodology since the 1980s, including “ambulatory assessment,” “experience sampling method,” or “real-time data capture.” Even though the terms differ, these approaches have the data collection in common (e.g., symptoms, behaviors, physiological processes, or daily life circumstances) while the participant undergoes normal activities. Therefore, this allows the interplay between contextual stressors, psychological distress, and maladaptive behaviors to be modeled (26). Compared to traditional measures using paper–pencil questionnaires, EMA is regarded as having many benefits for addiction research, including decreased recall bias, decreased contextual bias (25, 27), and increased validity to model the temporal sequence of events between risky situations, craving, and substance use (28, 29). Although such tools have been available for over 30 years, the emergence of smartphone applications as a platform for EMA greatly improved the acceptability and usability of this technology (30). In the last decade, EMA systems have been developed for adolescents with addictions (31) and applied to the assessment of psychiatric symptoms in outpatients with internalizing/externalizing disorders (32–36). In contrast with adults [e.g., Ref. (37)], EMA has not yet been assessed, to our knowledge, for studying the relationship between psychiatric symptoms and patterns of substance use in adolescents. In addition, the feasibility of using EMA in adolescents with severe psychiatric symptoms remains understudied.

The smartphone app Stop-Cannabis was developed in 2013 in Geneva, Switzerland with financial support from the local Health Department.^1^ The app aims to help users reduce or stop their cannabis use and prevent relapse. Stop-Cannabis consists of several modules based on cognitive behavioral therapy strategies, motivational interviewing, and relapse prevention programs. Particular effort has been made to include the principles of self-determination (autonomy, competence, and relatedness) (38) into the app and promote its customization (39). As in other studies (40–42), participant interaction and rewards support the playful aspect of the intervention. Personalization of the users’ goals and the app main screen may further contribute to increase adoption by user (43). The contents of the application are summarized below [and described in detail in Ref. (39)]. Since February 2013, the Stop-Cannabis app [available on Google Play (Android) and (iOS) App Store] has been downloaded more than 13,000 times, and the app is currently used by 1,000 people every month. The app was reported to have a good level of acceptability among community users in an online satisfaction survey (39).

This study is part of a general collaborative research program between the child and adolescent psychiatric department team and the addiction unit. The purpose of this wider program is to inform the difference in the trajectories of inpatients adolescents with SUDs compared to other and to help developing a better clinical practice (i.e., early detection, clinical assessment, and therapeutics).

### Objectives

The primary objective of our pilot study is to evaluate the feasibility and acceptability of two different digital tools (an EMA tool and Stop-Cannabis) based on smartphone apps in adolescents with dual disorders during a 1-year follow-up period after hospital discharge. We aim to determine the feasibility of the EMA, adherence to recommendations, and the quality of data collected using an EMA digital assessment tool. In addition, we aim to evaluate the feasibility, acceptability, and use of the Stop-Cannabis app, a digital intervention tool, during outpatient aftercare. The authors expect to obtain from this pilot study data on the feasibility and acceptability of two kinds of digital tools (one related to assessment and the other one to an intervention) possibly useful for adolescents with SUDs and comorbid severe psychiatric disorders.

Secondary objectives are (1) to estimate the prevalence of SUDs in adolescents with psychiatric disorders hospitalized in the Department of Child and Adolescent Psychiatry at the Pitié-Salpêtrière University Hospital, Paris, France (this department provides one-third of all child and adolescent inpatient beds in the Paris area); (2) to describe the clinical and psychosocial characteristics of substance users compared with non-users; (3) to determine the risk factors for the onset of SUDs during follow-up in participants without dual diagnoses at baseline; (4) to determine the risk factors for the persistence of non-cannabis SUDs during follow-up; (5) to document the longitudinal interplay between substance use and psychopathology in adolescents with dual diagnoses at baseline; and (6) to examine the association between the use of the Stop-Cannabis app and the patterns of substance use at 1-year follow-up in naturalistic settings to inform the potentiality for future research.

## Methods and Analysis

### Selection of Participants

#### Inclusion and Exclusion Criteria

Participants will be adolescents (11–18 years old) who are hospitalized in the Department of Child and Adolescent Psychiatry at the Pitié-Salpêtrière University Hospital between September 2016 and September 2018. The participants will be assessed at baseline. According to the presence or absence of comorbid SUDs, they will be included in either the SUDs group or the control group. The SUDs group will receive the mobile apps, whereas the control group will not. Exclusive tobacco consumption is not considered to be a criterion for inclusion in the SUDs group. Inclusion to the non-SUD control group will be made according to a match with adolescents from the SUDs group (for age, gender, inpatient unit, and time of admission). Exclusion criteria include non-French speaking, those without a personal mobile phone, lack of informed consent from parents or from the adolescents, and any mental or physical problems that interfere with participation in the study (e.g., autism with very low communication abilities, severe to profound intellectual disability, severe motor disability).

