#### Sample Size

A conservative approach was adopted for this feasibility study, which emphasizes descriptive and qualitative feedback. Consequently, based on the recommendations for pilot studies (44), we plan to include 80 participants (40 cases, 40 controls) over a 2-year inclusion period. As there are around 280 inpatient admissions per year in the Department of Child and Adolescent Psychiatry, i.e., *n* = 560 potential participants contacted at baseline during the 2 years, this will represent a 14% inclusion rate. We predict that the prevalence of SUDs will be similar to that previously reported (18). A good level of compliance with EMA and Stop-Cannabis is expected, consistent with previous studies that reported high levels of adherence (up to 80%) to similar tools in adolescents with comorbid psychiatric disorders (31, 45), and in adults with associated severe psychiatric disorders (32, 46). An acceptance rate of 80% is expected in the SUD group and 50% for the control group. A 50% retention rate at 1-year follow-up is anticipated based on previous longitudinal studies among adolescents (47). In case of a lower enrollment rate, we will either continue to enroll participants during an additional year (2019) in order to reach the intended sample size or use incentives (e.g., free participation in leisure and sport activities in groups) to encourage participant enrollment.

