##### Secondary Outcomes

(1)The prevalence of SUDs among adolescent inpatients will be assessed.(2)The clinical and psychosocial characteristics of participants with and without SUDs at baseline, including history of adverse childhood experiences, comorbid psychiatric diagnoses, and the level of functional impairment, will be compared.(3)The risk of developing SUDs among non-SUD adolescents during a 1-year follow-up period following hospital discharge will be investigated.(4)The proportion of inpatient adolescents with non-cannabis substance use at baseline whose SUDs persist at 1 year will be estimated.(5)We will explore how psychiatric symptoms could affect the pattern of substance use among SUDs participants.(6)We will assess whether specific patterns of Stop-Cannabis app use is associated with substance use outcomes at 1-year follow-up.

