##### Secondary Outcomes

(1)The number of inpatients with SUDs will be compared with the total number of adolescents admitted to the Department during the inclusion period.(2)Descriptive analyses of clinical and psychosocial variables will be conducted. Chi-square will be used to compare categorical variables, and Student’s *t*-test for continuous variables. A difference of *p* < 0.05 will be considered statistically significant.(3)Univariate logistic regression analyses will be performed to determine whether clinical features (as independent variables) predict the onset of SUDs at 1 year (as dependent variable) in the non-SUD control group and persistence or cessation in the SUD group. Possible mediators of this relation will be examined using the four-step approach proposed by Baron and Kenny (65), followed by a Sobel–Goodman test. In particular, we will test the mediation effect of the baseline impulsivity score, the baseline level of sensation-seeking (subscales of the UPPS-P score), and the baseline level of mood lability (ARI total score) on the relationship between psychopathology and SUDs.(4)Comparable analyses would be conducted to determine the clinical and psychosocial risk factors for the persistence of SUDs among those with non-cannabis substance use at baseline.(5)Specific analyses based on mixed-effect models (a random effect for participants and fixed effects for time) will be performed to examine the interplay between the pattern of substance use, psychiatric symptoms, and contextual stressors for treating EMA data [as in Ref. (45, 66)]. In line with previous recommendations, data will be studied at the daily level (with average ratings), at the concurrent momentary level, and at the prospective level using both linear and non-linear modeling (32). These analyses will be performed and presented separately between those with cannabis use disorder and the other participants to prevent any interference due to the use of the Stop-Cannabis app.(6)Correlational analyses will be carried out to examine the association between the level of app use (EMA or Stop-Cannabis) (i.e., mean percentage of random prompts, mean percentage of days assessment completed) and participant’s clinical outcome at follow-up (i.e., frequency of substance use and level of functional impairment at 1 year).

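### Controls are matched to SUD cases on four factors, but the baseline group comparison names tests for independent groups and does not account for the matching; if matching is individual, those tests are conservative

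*Protocol article*

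**What the plan says.** Under Inclusion and Exclusion Criteria, the Protocol article states: "Inclusion to the non-SUD control group will be made according to a match with adolescents from the SUDs group". The factors are given as "for age, gender, inpatient unit, and time of admission". It does not say whether each control is tied to one particular case or whether the control group is balanced as a whole.

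Under Sample Size: "we plan to include 80 participants (40 cases, 40 controls) over a 2-year inclusion period". The number is "based on the recommendations for pilot studies (44"); no effect size, standard deviation or power is attached to the case-control contrast.

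The contrast is item (2) of the secondary outcomes, which will compare "The clinical and psychosocial characteristics of participants with and without SUDs at baseline". Item (2) under Statistical Methods fixes the tests and the threshold: "Chi-square will be used to compare categorical variables, and Student’s *t*-test for continuous variables", and "A difference of *p* < 0.05 will be considered statistically significant".

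No section carries the matching into the analysis. The regression adjustment mentioned under Limitations concerns adherent against non-adherent participants, not cases against controls.

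**The concern.** Chi-square and Student's t-test, named together without qualification, are ordinarily read as tests for two independent samples. Matching makes the samples dependent. To the extent that age, gender, unit and admission time predict an outcome, matched participants resemble each other on it. A test that ignores this leaves the shared variation in its standard error, so it is less precise than the design allows.

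Objective (2) is worded as descriptive, but the article sets a significance threshold for it. Its section on anticipated results also predicts significant associations of SUDs with psychiatric disorders, and higher impulsivity, mood dysregulation and sensation-seeking in the SUD group. Controls receive neither app and no EMA, so this contrast is one of the main uses of half the sample. The risk is that a real difference is reported as not significant, and that the effort of matching yields less than it could.

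**Working it through.** **The article's own figure.** The only arithmetic attached to the sample size is the inclusion rate: 80 / (2 × 280) = 80/560 = 14.3%, which agrees with the stated 14%. No power figure exists to reproduce.

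**Inputs from the article.** 40 cases and 40 controls (Sample Size); threshold 0.05 (Statistical Methods, secondary item 2).

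**Assumptions, not in the article.** Individual 1:1 matching with 40 intact pairs; two-sided tests; a true difference of 0.5 SD for scores, or 30% against 60% for a binary variable; within-pair correlation ρ from 0 to 0.3.

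**Standard error.** With SD = 1 and n = 40 pairs:

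- The unpaired test uses √(2/n) = √(2/40) = 0.224, whatever ρ is.
- The true standard error of the difference is √(2(1 − ρ)/n). For ρ = 0.1, 0.2 and 0.3 this is √0.045 = 0.212, √0.040 = 0.200 and √0.035 = 0.187.
- The ratio is 1/√(1 − ρ) = 1.05, 1.12 and 1.20.

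**Type I error.** Under no difference, the unpaired statistic has standard deviation about √(1 − ρ), not 1. The actual level is therefore about 2Φ(−1.96/√(1 − ρ)). At ρ = 0.3 this is 2Φ(−2.34) ≈ 1.9%.

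**Power.** The normal approximation for the unpaired test at ρ = 0 is Φ(0.5/0.224 − 1.96) ≈ 61%. Simulation (40,000 data sets per setting) gives:

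| ρ | SE overstated by | Actual type I error, unpaired t | Power, unpaired t | Power, paired t |
|---|---|---|---|---|
| 0 | 0% | about 5% | 60% | 59% |
| 0.1 | 5% | 3.9% | 61% | 64% |
| 0.2 | 12% | 2.9% | 61% | 69% |
| 0.3 | 20% | 1.9% | 62% | 74% |

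The power forgone is therefore nil at ρ = 0 (where pairing costs about 1 point), then about 3, 8 and 12 points.

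**Binary variables.** For 30% against 60%, with ρ now the correlation of an underlying normal variable (20,000 data sets per setting), chi-square against McNemar gives 80 vs 78% at 0, 80 vs 80% at 0.1 and 82 vs 85% at 0.3. With 40% in both groups, the type I error of chi-square is 5.2%, 4.6% and 3.1%. The loss is smaller than for scores.

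**What ρ means here.** If the pair resemblance comes only from the matching factors, ρ is roughly the share of outcome variance that those factors explain. A ρ of 0.3 would need them to explain about 30%. Nothing in the article supports or excludes that.

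**The case against.** The strongest reply is that individual pairing is inferred. The article speaks only of a match, never uses the word *unpaired*, and gives a 40:40 split that suits 1:1 matching but also suits frequency matching, for which paired t and McNemar would be the wrong tools. This stands, and the table above applies only to individual pairs. It does not remove the point: under frequency matching the analysis should adjust for the matching factors, and none is stated.

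A second reply is that one sentence on a descriptive comparison leaves detail to the SAP. That would answer silence. Here the article names the tests and the threshold, and those tests do not fit the design it also names.

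A third is that the study is a pilot with no power claimed for this contrast, that the error is in the safe direction, and that the loss is negligible for low correlation and for many categorical variables. All of this is correct and limits the severity.

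A reader might also draw stronger conclusions that the article does not support:

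- *Case-control odds ratios will be biased towards 1.* No such odds ratio is planned in item (2). The logistic models in items (3) and (4) concern onset among controls, and persistence among those with SUDs or non-cannabis use, so they do not estimate the matched contrast.
- *The matching variables will themselves be tested between groups.* Item (2) concerns clinical and psychosocial variables; age and gender are listed separately as sociodemographic data, and no test of the four factors is clearly planned.
- *Significant findings will be unreliable.* The opposite holds: the false-positive rate falls below 5%.

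**Conclusion.** The mismatch is real and limited. The article matches on four factors and then fixes tests that take no account of the matching. If matching is individual, those tests are conservative: for a 0.5 SD difference the loss of power runs from nil at ρ = 0 to about 12 points at ρ = 0.3, and it is smaller for binary variables. These sizes rest on 40 intact pairs, two-sided 5% tests and an assumed ρ.

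Only secondary objective (2) is affected. The primary outcomes on feasibility, acceptability and EMA validity do not use the matched contrast. Severity is minor to moderate.

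**What to change.** State whether matching is individual (and in what ratio) or by frequency. If individual, record the pair identifier from enrolment, since it may be hard to rebuild later. Then replace the test wording in item (2):

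- **Individual pairs:** paired t-test, or a mixed model with a pair effect, for scores; McNemar or conditional logistic regression for categories.
- **Frequency matching, or pairs that break:** regression of each characteristic on group, with age, gender, unit and admission period as covariates.

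The cost is a few sentences and one data field. No extra participants or assessments are needed, because the matching factors must be known in order to match. If the correlation turns out to be zero, a paired t-test gives up about 1 point of power in the example above.
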